**1.3.3.3.2. XL880-002**

As of 20 August 2007, 24 subjects in study XL880-002 (A Phase 1 Dose-Escalation Study of the Safety and Pharmacokinetics of GSK1363089 Administered Orally Daily to Subjects With Solid Tumors) have been treated across four different dose levels (60 mg/day [6 subjects], 80 mg/day [9 subjects], 120 mg/day [3 subjects], and 100 mg/day [3 subjects]). Two subjects dosed at 120 mg/day had DLTs (one with Grade 3 hypertension, one with Grade 3 dehydration) and required dose delay and reduction. 80mg once daily was determined to be the MTD on this study.

A total of 278 AEs have been reported for the 24 subjects enrolled in this ongoing Phase 1 dose-escalation study of daily administration of GSK1363089. Eighteen of 24 (75%) subjects reported at least one AE. Most (254/278, 91%) of the AEs reported were Grade 1 or 2 in severity, though a total of 17 Grade 3 and 2 Grade 4 events were reported. A total of 9/24 (37.5%) subjects had events of Grade 3 or higher. Grade 4 events were elevated GGT and pulmonary embolus, of which elevated GGT was considered GSK1363089-related. Grade 3 events were: dyspnea (2 subjects) and the following all occurring in one subject each with events not related unless noted: diarrhea (related), heparin-induced thrombocytopenia, perirectal abscess, post-procedural hemorrhage, blood alkaline phosphatase increased (related), blood calcium decreased (related), blood phosphorus decreased (related), electrocardiogram QT corrected interval prolonged, elevated GGT, increased lipase (related), dehydration (related), confusional state, renal failure (related), and hypertension (related). Many of these events were laboratory abnormalities without associated symptoms. A total of 100/278 (36%) events in 15 (63%) subjects were assessed as possibly or probably related to study treatment. Of the related events eight were Grade 3 and one was Grade 4 (GGT elevation).

Twenty one serious adverse events were reported in ten subjects. Four events in three subjects were assessed as possibly or probably related to study treatment including confusional state (Grade 3), dehydration (Grade 3), and hypertension (Grade 3) and elevated creatinine (Grade 2) in one subject.

#### **1.3.3.3.3. MET111644 (Formerly XL880-201)**

A total of 105 AEs in 16 subjects have been reported as of 20 August 2007. Nine (56%) subjects reported at least one AE. The AEs, regardless of relationship with GSK1363089, reported in  $\geq 10\%$  of subjects are the following: hypertension (6 subjects, 38%); diarrhea, fatigue, headache, and nausea (each reported in 3 subjects, 19%); and dizziness, dysphonia, and vomiting (each reported in 2 subjects, 13%).

The majority (66 of 105) of AEs reported were of Grade 1. Nineteen events were of Grade 2, nine events were of Grade 3, two events were of Grade 4. No Grade 5 events were reported, and nine events were not assigned a grade. The Grade 3 events were: atrial flutter, pain in extremity, renal hemorrhage, dyspnea, pulmonary embolism, deep vein thrombosis (one event each), and three cases of hypertension. The two Grade 4 events were renal cell carcinoma and depression.

A total of 62 of the 105 events (59%) were considered possibly or probably related to GSK1363089. Eight of the 16 subjects (50%) reported at least one related event. The majority of these related events were of Grade 1 (45 of 62 events), 13 were of Grade 2, and three were of Grade 3. No Grade 4 or 5 related events were reported. Related AEs reported in  $\geq 10\%$  of subjects (2 subjects) were the following: hypertension (7 subjects,

44%), and diarrhea, fatigue, dizziness, and headache, in two subjects each (13%). The only Grade 3 events considered possibly or probably related to GSK1363089 were the events of hypertension in 3 subjects (19%). There were no AEs leading to withdrawals from the study.

Fifteen serious adverse events have been reported in three subjects as of 24 August 2007. Two events of vomiting in one subject were assessed as related to study drug GSK1363089.

One death from progressive papillary renal cell carcinoma that occurred within the 30 days from last administration of GSK1363089 was reported on MET111644. The event was assessed as not related to study treatment. In addition, one subject died 62 days after last study drug administration, following prior discontinuation from the study due to disease progression.

#### **1.3.3.4. GSK1363089 Clinical Pharmacokinetics**

In XL880-001, the Phase 1 study of the Intermittent 5&9 dosing schedule, results from non-compartmental PK analysis indicated relatively rapid absorption of GSK1363089, with median peak concentrations occurring at about 4 hours after dose administration, independent of dose and PK study day. Over the 0.1 to 4.5 mg/kg dose range studied, AUC and Cmax increased in a roughly dose-proportional manner, particularly at doses greater than 1.4mg/kg (~100mg). Concentration-time profiles typically displayed monoexponential decay after attainment of Cmax. In the largest dose cohort (N=14) at the MTD dose of 3.6mg/kg (median 240mg), the median elimination t1/2 was 34 hours (range: 23 – 61 hours).

In XL880-002, the Phase 1 study using the once-daily dosing schedule, PK results are similar to those from XL880-001. Estimates of multiple-dose accumulation ratios based on pre-dose concentrations at various times during the first 28 days of dosing, the median elimination t1/2 at the MTD dose of 80mg once daily was 48 hours (range 22 – 72 hours).

#### **1.3.3.5. GSK1363089 Clinical Observations in Study XL880-001**

In Study XL880-001, efficacy is an exploratory objective; however, of the 40 subjects, there have been five subjects with partial responses (PRs): three subjects with papillary renal carcinomas and two subjects with thyroid carcinoma. Four additional subjects have had a decrease in tumor measurements not reaching the 30% Response Evaluation Criteria In Solid Tumors (RECIST), and seven other subjects have had stable disease (SD) for >3 months. In this population, these findings are suggestive of anti-tumor activity and warrant further investigation in more defined populations.

#### **1.3.3.6. GSK1363089 Clinical Pharmacodynamics**

Immunohistochemical analyses of tumor biopsies taken at baseline from three subjects in the XL880-001 clinical trial indicated high expression of c-MET and RON, with a high percentage (approximately 70%) of constitutively activated phospho-c-MET and phospho-RON. Increased labeling of phospho-ERK, phospho-Akt, and Ki67 (a marker of cell proliferation), and decreased apoptotic activity (assessed by terminal deoxynucleotide transferase-mediated dUTP nick-end labeling [TUNEL]), was also observed. In three subjects examined after treatment with GSK1363089 on an Intermittent 5&9 dosing schedule, a marked inhibition of phosphorylation of c-MET, RON, ERK, and Akt associated with a decrease in Ki67 and an increase in TUNEL labeling was observed. These effects were observed as early as after the first five daily doses and at doses as low as 0.8 mg/kg. These results suggest a decrease in proliferation and an increase in apoptosis in tumor cells after GSK1363089 treatment, consistent with the putative mechanism of action of GSK1363089. In one subject, two sets of biopsies were collected: at dosing Cycles 1 and 6. The magnitude of the effect observed after six treatment cycles was more pronounced than after one cycle, suggesting a cumulative effect over time.

### **1.4. Rationale**

#### **1.4.1. Rationale for the Study and Study Design**

Gastric cancer remains one of the most common types of cancer in the world today. The clinical outcome for this malignancy remains poor, with a 5-year survival rate of only about 20% (all stages). The primary curative option in this clinical scenario is surgical excision. However, a significant unmet medical need exists for patients with unresectable gastric cancer because no effective therapy has yet been identified.

GSK1363089 is a new chemical entity that inhibits multiple RTKs with growth-promoting and angiogenic properties. The primary targets of GSK1363089 are the HGF and VEGF RTK families (e.g., c-MET VEGFR2/KDR, PDGFR).

Because amplification of *c-MET* has been associated with the pathogenesis of gastric cancer, inhibition of c-MET receptor activation by agents such as GSK1363089 may be of therapeutic benefit in this patient population.

#### 1.4.2. Rationale for Dosage Selection

Subjects will be enrolled into one of two cohorts in this study:

- Cohort 1 – Intermittent 5&9 dosing; 240mg per dosing day;
- Cohort 2 – Daily dosing; 80mg per dosing day

The dose and schedule for Cohort 1 in this study are based on safety, PK, and pharmacodynamic data and clinical observations from the ongoing Phase 1 study, XL880-001, in which subjects are being dosed using the Intermittent 5&9 dosing regimen. Similarly, the dose and schedule for Cohort 2 in this study are based on safety, PK, and pharmacodynamic data and clinical observations from the ongoing Phase I study, XL880-002, in which subjects are being dosed using the daily dosing regimen.

Subjects in XL880-001 treated at nominal doses of up to 3.6 mg/kg have tolerated GSK1363089 well, with no DLTs. Adverse events that may potentially be associated with GSK1363089 administration (fatigue and hypertension) have been mild to moderate in severity, reversible, and managed with either additional medication (e.g., antihypertensives) or dose delay and/or reduction. Clinical signs (e.g., hypertension, proteinuria) and exploratory pharmacodynamic analyses suggest that modulation of VEGFR and/or c-MET likely occurs following administration of doses  $\leq 3.6$  mg/kg.

Based on preliminary PK analyses from XL880-001, fixed dosing is not expected to result in any greater variability in exposure than dosing based on body mass. In study XL880-001, subjects had nominal mass-based doses. Actual doses administered were based on the range into which an individual subject's weight fell. Weight ranges were  $<60$  kg,  $\geq 60$  to  $<80$  kg,  $\geq 80$  to  $<100$  kg, and  $\geq 100$  kg. The dose for subjects weighing  $\geq 60$  to  $<80$  kg in the 3.6-mg/kg dosing cohort was 240 mg per dosing day. Therefore, a regimen of 240 mg per dosing day administered on an Intermittent 5&9 dosing schedule is expected to be safe and potentially efficacious in subjects with metastatic gastric carcinoma or adenocarcinoma of the gastroesophageal junction or of the distal esophagus.

In the XL880-002 study, GSK1363089 was tolerated when administered for 28 days at doses up to 80 mg/day. Adverse effects include hypertension, fatigue, nausea, vomiting, and asymptomatic changes in laboratory values. The MTD for daily GSK1363089 dosing has been determined to be 80 mg/day. Based on preliminary PK analysis, GSK1363089 accumulates in plasma with repeated daily dosing. Results from pharmacodynamic analyses of plasma and surrogate tissue biomarkers indicate potential biological effects of

GSK1363089 in subjects. Anti-angiogenic pharmacodynamic marker changes have been detected in this clinical trial consistent with effects reported with other anti-angiogenic agents. The clinical observations of decreased tumor size, prolonged stable disease and/or improvement in tumor markers are consistent with the antitumor activity observed in XL880-001. These findings suggest that GSK1363089 dosed daily may have broad antitumor activity.

The 14-day MTD of GSK1363089 in both XL880-001 (Intermittent 5&9 regimen) and XL880-002 (daily regimen) is similar, with 1200mg (240mg x 5) and 1120mg (80mg x 14) administered over 14 days leading to very similar AUC(0-336h) of 14910 and 15110ng\*hr/mL, respectively. Adding a cohort of subjects treated with the daily regimen will allow characterization of the safety, efficacy, and levels of exposure provided by two schedules of GSK1363089, as well as an exploration of whether the intermittent 5&9 regimen provides suboptimal exposure over time and whether continuous exposure provide better efficacy.

## **2. STUDY OBJECTIVES**

The primary objectives of this study are as follows:

- To determine the confirmed response rate of GSK1363089 treatment in subjects with gastric carcinoma or adenocarcinoma of the gastroesophageal junction or of the distal esophagus.
- To further evaluate the safety and tolerability of GSK1363089.

The secondary objectives of this study are as follows:

- To assess the disease stabilization rate, progression-free survival, duration of stable disease, and overall survival in subjects with gastric carcinoma or adenocarcinoma of the gastroesophageal junction or of the distal esophagus who are treated with GSK1363089.
- To characterize the PK and pharmacodynamic parameters of GSK1363089 in subjects with gastric carcinoma or adenocarcinoma of the gastroesophageal junction or of the distal esophagus.

Note: Each of the primary and secondary study objectives will be assessed for each dosing Cohort (1 – Intermittent 5 days on/9 days off dosing; 2 – daily dosing) separately and together.

The exploratory objectives of this study are as follows:

- To characterize the *c-MET* amplification status of patients in this study population and possible associations with response to GSK1363089 therapy. In addition, the mutational status as well as expression of *c-MET* and related genes and proteins (e.g., RON) and of relevant downstream targets may also be assessed.
- To evaluate the efficacy and safety profiles between two GSK1363089 dosing regimens - Intermittent 5 days on/9 days off and daily.
- To evaluate the effect of GSK1363089 treatment on potential pharmacodynamic markers of clinical activity in paired tumor biopsies (e.g. phospho-MET).

### **3. STUDY DESIGN**

#### **3.1. Overview of Study Design**

This is a Phase 2, non-randomized, sequential-cohort, open-label, single-stage, safety and efficacy study, with an initial cohort of subjects enrolled onto the Intermittent 5&9 regimen, and then a 2nd cohort of subjects enrolled onto the daily regimen. Enrolment into Cohort 2 will not begin until enrolment into Cohort 1 has completed.

The estimated length of the study is 40 months for subject accrual and treatment. This study consists of a Pre-Treatment Period (screening and baseline evaluations), a Study Treatment Period, an optional Treatment Extension Period, and a Post-Treatment Period (including an end-of-treatment visit and an extended follow-up period). Throughout the study, AEs will be recorded as volunteered. Adverse events will be graded according to the NCI CTCAE v3.0. A copy of this grading scale will be provided to the study sites upon request, or it can be accessed at <http://ctep.cancer.gov/reporting/ctc.html>. All doses of GSK1363089 are to be administered on an empty stomach.

##### **3.1.1. Pre-Treatment Period**

Subjects will undergo evaluations to determine study eligibility. Screening will be conducted within 28 days before initial treatment on Day 1. The following baseline evaluations must be done within 72 hours of the initial treatment: physical examination, measurement of vital signs, the Eastern Cooperative Oncology Group (ECOG) performance status (Appendix B), hematology, serum chemistry panel, urinalysis, and a pregnancy test (in women of childbearing potential). In addition, the appropriate arrangements must be made to ensure that 10 unstained slides or a paraffin block of archived tumor tissue are shipped to the central analysis laboratory, no later than 14 days after the subject's first dose of study drug.

It is important to note that in the event that enrolment of 30 evaluable subjects in Cohort 2 is completed before the target of 4 subjects with *c-MET* amplification, as defined by  $\geq 2$  copies of *c-MET* per copy of chromosome 7 (see Section 3.3.1 for full definition), has been reached, then extra subjects, with proven *c-MET* amplification, pre-screened by FISH, will be enrolled in the study, until the target is reached. In this instance, 10 unstained slides or a paraffin block of tumor tissue must be shipped to the central analysis laboratory as soon as possible after the subject signs the consent form. The subject will not be able to start the study treatment period until FISH results are available, and then only if they have *c-MET*-amplified tumor, as defined by  $\geq 2$  copies of *c-MET* per copy of chromosome 7.

### **3.1.2. Study Treatment Period**

Treatment will be administered on an outpatient basis. Previously reported AEs and potential risks for GSK1363089 are described in Section 5.11. Dose modifications for GSK1363089 are described in Section 3.4. No investigational or commercial agents or therapies other than those described in Section 4.4 may be administered with the intent to treat a subject's malignancy.

GSK1363089 will be administered at a dose of 240 mg on an Intermittent 5&9 dosing schedule in Cohort 1; and at a dose of 80 mg on a daily dosing schedule in Cohort 2. Each treatment cycle will be 2 weeks in duration. The 8-week Study Treatment Period will consist of four 2-week treatment cycles. Laboratory evaluations and physical examinations will be conducted before each dosing cycle. GSK1363089 treatment will be stopped if there is disease progression at any time.

In-patient hospitalization is not required for study treatment and assessments if the subject is adequately observed and procedures are performed as specified herein.

At specified timepoints during the treatment period, AEs will be solicited by asking the subject, "Are you having any new symptoms?" Answers will be recorded on the AE case report form (CRF) page. Tumor assessment will be performed at the end of the Study Treatment Period (8 weeks).

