### **Statistical Methods**

The primary efficacy endpoint is objective response rate (ORR). ORR will be estimated for the safety and the evaluable populations. A corresponding exact 95% confidence interval will be calculated.

Secondary efficacy endpoints are disease stabilization rate (DSR), progression-free survival (PFS), duration of stable disease, and duration of overall survival (OS). DSR will be summarized using a point estimate of the proportion and the exact 95% confidence interval. PFS, OS, and duration of stable disease will be summarized using Kaplan-Meier methods.

For the primary safety endpoint, AEs and serious adverse events (SAEs) will be tabulated by system organ class and preferred terms. Laboratory test results after the first dose will be summarized using change from baseline values and shift from baseline tables.

Each endpoint will be assessed both in the combined Cohorts and in each Cohort separately.

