## 5.2. Pre-Treatment Period

Informed consent must be obtained before any study-specific tests or evaluations are conducted.

The screening visit will occur within 28 days before administration of study drug and may serve as the baseline evaluations if done within 72 hours of initial dosing. Study eligibility will be based on fulfilling all study inclusion and exclusion criteria. The investigator will use clinical judgment when determining the clinical significance of laboratory values at baseline and throughout the study.

At the screening visit, information will be collected and subjects will have clinical evaluations as follows:

- Informed consent
- Demographics
- Medical and cancer history
- Physical examination, including measurements of height and weight
- Vital signs (5-minute sitting BP, pulse, respiratory rate, oral temperature)
- ECOG performance status assessment ([Appendix C](#))
- Prothrombin (PT)/partial thromboplastin (PTT) times or International Normalized Ratio (INR)

- Clinical laboratory tests (hematology, serum chemistry panel, urinalysis) (see Section 5.6)
- 12-Lead electrocardiogram (ECG) (see Section 5.6.6)
- If a subject presents with abnormal ECGs or clinical symptoms, either or both of which are suggestive of a decreased ejection fraction, then he or she is to be evaluated by cardiac imaging (ECHO or MUGA) for determination of cardiac function prior to enrolment. The results should be discussed with the GSK Study Physician to decide whether the subject can be enrolled
- ACTH stimulation test (see Section 5.6.3)
- Thyroid function tests (TSH, Free T3 and T4) (see Section 5.6.4)
- Ocular assessments – the following examinations must be performed in all subjects (see Section 5.6.5):
  - Best corrected visual acuity
  - Goldman visual field evaluation
  - Measurement of intraocular pressure
  - Slit lamp examination
  - Dilated fundoscopic examination including full field color retinal photographs
- Ocular assessments – the following examinations must be performed in subjects who report poor vision in low illumination or have other symptoms suggestive of night blindness (see Section 5.6.5):
  - Light-dark adaptation testing
  - International Society for Clinical Electrophysiology of Vision (ISCEV) standard Electroretinography (ERG)
  - Cancer-associated retinopathy (CAR) antibody testing

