## **7. SAFETY**

### **7.1. Adverse Events and Laboratory Abnormalities**

#### **7.1.1. Clinical Adverse Events**

An AE is any untoward medical occurrence in a patient or clinical investigation subject administered a pharmaceutical product whether or not it is considered drug related. This would include any side effect, injury, toxicity, sensitivity reaction, abnormal or worsening of a laboratory value, concurrent illness or sudden death. Pre-existing conditions that worsen during a study will be reported as AEs. Toxicity grade will be defined according to the NCI CTCAE v3.0 (<http://ctep.cancer.gov/reporting/ctc.html>).

The relationship of the AE to the Investigational Drug will be based on the following four definitions, as assessed by the investigator:

1. Not Related

The AE is ***clearly not related*** to the Investigational Drug because the AE is attributed to an alternate cause(s).

2. Unlikely Related

The AE is considered *doubtfully related* to the Investigational Drug. The AE is not temporally related to the administration of the Investigational Drug, and other factors provide a more plausible explanation of the AE.

3. Possibly Related

The AE *may be related* to the Investigational Drug. The AE is temporally related to the administration of the Investigational Drug, and there are facts to support a causal relationship between the AE and the Investigational Drug; however, other causal explanations for the AE also exist.

4. Probably Related

The AE is *likely related* to the Investigational Drug. The AE is temporally related to the administration of the Investigational Drug and is more likely explained by exposure to the Investigational Drug than by other factors or causes.

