#### **8.1.4. Safety Analysis**

Safety endpoints include adverse events, laboratory data, and concomitant medications.

Adverse event verbatim terms recorded on the CRF will be mapped to preferred terms using the Medical Dictionary for Regulatory Activities (MedDRA).

A treatment emergent adverse event (TEAE) is defined as any adverse event with an onset date on or after date of first dose of study drug, or any ongoing event on date of first dose that worsens in severity after date of first dose. Only TEAE's with an onset date prior to date of last dose + 30 days will be tabulated in the summary tables.

TEAEs will be summarized for overall incidence, worst reported severity, and relationship to study treatment according to system organ class and preferred term.

Laboratory variables will be categorized according to the CTCAE v3.0 and will be summarized using mean change from baseline and shift in category from baseline.

All concomitant medications collected on the CRF's will be mapped to the WHO dictionary. Prior and concomitant medications will be summarized separately by ATC Level and Preferred Term.

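### The scripted AE question asks only about new symptoms, although worsening also counts as an AE and a TEAE, and no pre-dose symptom grade is scheduled: a risk of under-ascertainment of unknown size

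*Combined protocol and SAP*

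**What the plan says.** - **Elicitation.** Section 3.1.2 gives the only scripted wording: "AEs will be solicited by asking the subject, 'Are you having any new symptoms". Section 3.1 names a second route: "Throughout the study, AEs will be recorded as volunteered". The protocol does not say how the two fit together.
- **Definition of an AE.** Section 7.1.1: "Pre-existing conditions that worsen during a study will be reported as AEs".
- **Definition of a TEAE.** Section 8.1.4 counts events that start on or after the first dose, and also "any ongoing event on date of first dose that worsens in severity after date of first dose".
- **Use of the data.** Safety and tolerability is a primary objective (Section 2). The synopsis, under Statistical Methods, says: "For the primary safety endpoint, AEs and serious adverse events (SAEs) will be tabulated by system organ class and preferred terms". Section 8.1.4 adds that "TEAEs will be summarized for overall incidence, worst reported severity, and relationship to study treatment".
- **Information before the first dose.** Screening (Section 5.2) lists "Medical and cancer history" with no grading stated. The Day 1 pre-dose list (5.3.1.1) has a symptom-directed examination and ECOG status but no AE item. AEs first appear in the Day 1 post-dose list (5.3.1.3), and the adverse-event row of Appendix A is blank at Screening and Baseline.

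**The concern.** The question is narrower than the endpoint it feeds. It asks about one of the two kinds of TEAE, and only about symptoms the subject has at that moment. A subject who enters with Grade 1 fatigue and is at Grade 3 by Day 29 can truthfully answer no. So can a subject whose vomiting came and went since the last visit. If that worsening is reported by another route, the plan has no scheduled record of the starting grade against which to judge it.

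The protocol's own text shows that this is not a rare situation. Eligibility allows ECOG status up to 2, and Appendix C describes grade 1 as symptomatic but ambulatory. Residual Grade 1 toxicity from earlier treatment is also allowed (exclusion 4). The related AEs listed in Section 5.11 include fatigue (25%), nausea (18%) and vomiting (14%), all of which depend largely on what the subject says. At stake are the incidence and worst-severity tables that answer the primary safety objective.

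**Working it through.** The documents state no figure for AE capture, so there is nothing of the plan's own to reproduce. The check sets the sections side by side.

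**1. Question against definitions**

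| Event | AE (7.1.1) | TEAE (8.1.4) | Asked about in 3.1.2 |
|---|---|---|---|
| New symptom, present at the visit | yes | yes | yes |
| New symptom, resolved before the visit | yes | yes | no |
| Symptom present at first dose, worse at the visit | yes | yes | no |
| Symptom present at first dose, worsened and then settled before the visit | yes | yes | no |

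Laboratory worsening does not depend on the question: Section 8.1.4 summarizes it by change and category shift from baseline.

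**2. Reference grade.** The worsening limb of the TEAE definition needs the severity at first dose. Going through Sections 5.2 and 5.3.1.1 and Appendix A, no pre-dose item calls for a CTCAE grade of ongoing symptoms. The nearest is exclusion 4 (Section 4.3), which requires grading of residual AEs from drugs given more than 21 days before enrolment. It serves eligibility, gives no instruction to keep the grade as a baseline, and does not cover symptoms of the cancer. Exclusion 3 allows chemotherapy to end 14 days before the first dose, so toxicity from treatment between 14 and 21 days earlier may also fall outside it.

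**3. Present tense against the visit calendar.** Section 3.1.2 does not list its timepoints; I take them to be the visits with an AE item. Cohort 1 doses on Days 1–5, 15–19, 29–33 and 43–47, with AE items on Days 1, 5, 15, 29, 43 and 47 and in Week 8. In the second and third dosing blocks the only AE visit is on the first day. The next comes 29 − 19 = 10 and 43 − 33 = 10 days after the last dose of the block (each visit ±3 days). Cohort 2 has AE items on Days 1, 8, 15, 29 and 43 and in Week 8, all under daily dosing. A question about current symptoms could therefore miss more short-lived toxicity in Cohort 1, although the documents do not show that it does.

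**4. Direction and possible scale (assumed values only).** For one symptom, let b be the share of subjects who have it at first dose, i the risk of new onset in the others, w the risk of worsening in those who have it, and c the share of worsening captured by any route. Then

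reported proportion = (1 − b)·i + b·w·c.

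The documents give none of these four values. With i = w = 0.30 and n = 30, the true expected count is 30 × 0.30 = 9.0. The reported counts are:

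| b | c = 1 | c = 0.5 | c = 0 |
|---|---|---|---|
| 0.20 | 9.0 | 8.1 | 7.2 |
| 0.40 | 9.0 | 7.2 | 5.4 |
| 0.60 | 9.0 | 6.3 | 3.6 |

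For example, b = 0.40 and c = 0.5 gives 30 × (0.60 × 0.30 + 0.40 × 0.30 × 0.5) = 30 × 0.24 = 7.2. The loss is zero if all worsening is captured and grows as c falls. The table shows how the mechanism works; it does not estimate this trial's loss.

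**The case against.** The strongest reply is that the script is only one route. Section 7.1.1 requires worsening to be reported, Section 3.1 records volunteered AEs throughout the study, and examinations and ECOG status recur during treatment. Section 3.4 bases dose decisions on Grade 3 events, so investigators must assess severity whatever the question says. This stands. A reader might infer that the primary safety result does under-count worsening; the documents support only a risk, because c above could be close to 1.

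Second, a worsening entered as an AE with a post-dose onset date meets the first limb of the TEAE definition without any baseline grade, and none of the planned summaries subtracts one. This stands in part. Someone must still decide that the symptom has worsened, and the plan gives no recorded reference for that decision. The gap can also work the other way, by labelling an unchanged symptom as treatment-emergent, so the missing grade alone does not fix the direction of bias.

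Third, the CRF is not among the documents, and Section 8.1 leaves analysis detail to a separate SAP. A grade field may exist. The accurate statement is that a starting grade is not specified for symptoms, not that none is collected. A later SAP could not supply a grade that was never recorded.

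Two further inferences fail. Nothing says that collection differs by site: Sections 3.1 and 3.1.2 apply to every site. The two sections also need not conflict, since volunteered and solicited reports can complement each other; what is missing is a sentence saying so.

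**Conclusion.** The point holds as a risk. The scripted question is narrower than the AE and TEAE definitions, and the worsening limb of the TEAE definition has no scheduled reference grade for symptoms. If sites follow the text literally, symptomatic worsening and events that resolve between visits may be under-ascertained in the primary safety endpoint. The effect of the question is downward whenever other routes miss some of these events. Its size is unknown, because the documents give neither the prevalence of symptoms at entry nor the share of worsening recovered by other routes. Laboratory safety results, the sample size and the response-rate error rates are untouched. The change is worth making because it is specific and cheap and concerns a primary objective, not because a distorted result has been shown.

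**What to change.** 1. In Section 3.1.2, replace the question with: 'Since your last visit, have you had any new symptoms, or have any symptoms you already had become worse?'
2. Reconcile 3.1 with 3.1.2 by stating that AEs are recorded throughout the study whether solicited, volunteered or observed. Keep the provision for volunteered reports: it is the only stated route that covers the whole study, and the script covers only timepoints during treatment.
3. Add to Section 5.3.1.1 and Appendix A a pre-dose Day 1 record of ongoing symptoms with CTCAE v3.0 grade, and name it in 8.1.4 as the reference for worsening in severity.

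**Cost.** One extra CRF entry at an existing visit, and slightly higher reported AE rates. The cohorts are sequential, so a change made after Cohort 1 would alter ascertainment mainly in Cohort 2. That difference should be noted wherever the cohorts' safety is compared (an exploratory objective in Section 2) or pooled (Section 8.1.1). For subjects already dosed, a missing starting grade would be hard to recover reliably, so the change is better made before further enrolment.
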